# A longitudinal, multi-centre, superiority, randomized controlled trial of internet-based cognitive behavioural therapy (iCBT) versus treatment-as-usual (TAU) for negative experiences and posttraumatic stress following childbirth: the JUNO study protocol

**DOI:** 10.1186/s12884-018-1988-6

**Published:** 2018-10-01

**Keywords:** Study protocol, iCBT, Immediate caesarean section, Negative birth experience, Postpartum haemorrhage, Posttraumatic stress following childbirth, PTSD following childbirth, PTSD

## Abstract

**Background:**

About one-third of women report their childbirth as traumatic and up to 10% have severe traumatic stress responses to birth. The prevalence of Posttraumatic stress disorder following childbirth (PTSD FC) is estimated to 3%. Women with PTSD FC report the same symptoms as other patients with PTSD following other types of trauma. The effect of psychological treatment for women with PTSD FC has only been studied in a few trials. Similarly, studies on treatment needs for women not diagnosed as having PTSD FC but who nevertheless face psychological problems are lacking.

**Methods/design:**

Women who rate their overall birth experience as negative on a Likert scale, and/or had an immediate caesarean section and/or a major postpartum haemorrhage are randomized to either internet delivered cognitive behaviour therapy (iCBT) plus treatment as usual (TAU) or TAU. The iCBT is to be delivered in two steps. The first step consists of six weekly modules for both the woman and her partner (if they wish to participate) with minimal therapeutic support. Step 2 consists of eight weekly modules with extended therapeutic support and will be offered to participants whom after step 1 report PTSD FC. Assessments will be made at baseline, 6 weeks, 14 weeks, and at follow-ups at 1, 2, 3 and 4 years after baseline. The primary outcome measures are symptoms of posttraumatic stress and depression. Secondary outcomes are quality of life, parent-child bonding, marital satisfaction, coping strategies, experience regarding the quality of care received, health-related quality of life, number of re-visits to the clinic and number of appointments for counselling during the 4 years’ period after the negative childbirth experience, time until the woman gets pregnant again, and the type of birth in the subsequent pregnancy. A health economic evaluation in the form of a cost utility analysis will be conducted.

**Discussion:**

This study protocol describes a randomized controlled trial that will provide information about the effectiveness of iCBT in women with negative experiences, posttraumatic stress, and PTSD FC.

**Trial registration:**

ISRCTN39318241. Date for registration 12/01/2017, retrospectively registered.

## Background

### Negative experiences following childbirth

Approximately 110,000 women give birth in Sweden annually [1]. Childbirth can be associated with both positive and negative psychological reactions, and a woman’s negative experience of labour and birth can affect her emotional wellbeing [2]. Between 9 and 45% of women reported a traumatic childbirth [3–5]. The experience of labour and birth is subjective, multidimensional and complex including physiological and psychological factors. There are several risk factors for negative childbirth-experiences such as unexpected medical problems, lack of social support, emotional state and care given during labour [2]. Negative and traumatic experiences during childbirth can sometimes lead to the development of posttraumatic stress symptoms and even posttraumatic stress disorder (PTSD).

### Posttraumatic stress following childbirth

In a meta-analysis, the prevalence for PTSD following childbirth (PTSD FC) was 3.1% among community samples and 15.7% among high-risk samples (e.g. pregnancy complications, emergency caesarean section, preterm birth) [6]. In a more recent review [7], the estimated prevalence was 2.4% among community samples, and 4.9% including both community plus high-risk samples when controlling for previous PTSD. The prevalence for clinically significant post-traumatic stress symptoms ranged between 9.6 and 27.3% [7]. The variation in prevalence rates may be explained by the timing and method used for assessment of PTSD criteria and symptoms [6, 7]. Prevalence rates were consistently higher in both studies when assessed close to childbirth. The prevalence rates above are based on the fourth edition of the Diagnostic and Statistical Manual for Mental Disorders (DSM-IV-TR) [8]. There is no sub-clinical or partial PTSD diagnose in DSM-IV, which is reflected in the heterogeneity regarding definition and label of clinically significant post-traumatic stress symptoms.

The definition of stressors for the development of PTSD according to DSM-IV can be applied to posttraumatic stress FC. A diagnosis of PTSD required affirming the following criteria: the stressor criterion (A) included stressful situations in which a person experience, witness, or is confronted with an event that involves actual death or threat of death or serious injury, or a threat to the physical integrity of self or others; the three symptom criteria re-experiencing (B), avoidance (C), and increased arousal (D); the duration criterion (E), and the influence criterion (F). Several risk factors are associated with PTSD FC, such as psychological factors (e.g. fear of childbirth), prepartum and partum factors (e.g. type of delivery) and postpartum factors (e.g. poor coping) [6, 9]. In a systematic review, five categories of risk factors for PTSD FC are identified: negative perception of childbirth, maternal mental health, history of trauma and PTSD, delivery mode and complications, and low social support [7].

Beside the symptoms of PTSD FC there is a strong association with postpartum depressive symptoms [6, 10] and comorbidity rates between 20 and 75% have been reported [10, 11]. Dysfunctional coping is common [12] and in terms of quality of life, women with PTSD FC reported negative changes in their mood, psychological well-being and social interaction [13]. PTSD FC and depression can also seriously affect the mother’s bonding with the baby with initial feelings of rejection towards the baby and in the long term she might develop either an avoidant or anxious attachment with her child [13]. Several aspects of infant development and behaviour, including patterns of eating, sleeping, and cognition, are mediated by parental posttraumatic reactions and depression [14]. Breastfeeding can also be negatively affected after a negative childbirth experience [15]. There is a higher risk of negative impact on the partner-relationship among women with PTSD FC than among women without. Sexual dysfunction and disagreements are common [13, 16] and those with PTSD FC and depression are more likely to avoid sexual relationships, wait longer before they get pregnant again, and give birth to fewer children [17, 18]. Few studies have examined the role of the partner and how his/her experience may affect the mother, the child, parenthood and any future plans to have more children [19]. It is suggested that providing additional support to partners in the early postpartum period may help alleviate any acute distress and reduce the detrimental impact the early postnatal symptoms may have on the partners [16]. Partner support seems important at all stages: stronger social partner support at mid-pregnancy was associated with lower emotional distress after childbirth [20] and stronger postnatal emotional partner support was associated with lower levels of symptoms of depression and hyper arousal [21].

### Interventions for women with negative experiences and PTSD FC

There has been relatively little research on psychological treatment for women with negative birth-experiences and PTSD FC [9]. The focus of this research has mostly been on postpartum counselling and debriefing (psychological interventions intended to reduce the psychological morbidity that arises after exposure to trauma). Results indicate that, in general, debriefing does not prevent psychiatric disorders or mitigate the effects of traumatic stress, even though people generally find debriefing helpful in the process of recovering from traumatic stress [22]. Gamble and Creedy [23] concluded that postpartum counselling and debriefing are often only general and nonspecific, and are not described in detail for replication. In addition, these interventions should be given by trained psychotherapists only. A systematic review [24] showed no preventive effect from a single debriefing session but did show some risk for developing PTSD. Postnatal debriefing should not be offered routinely after a traumatic birth [25].

The effects of structured writing assignments for psychological health have been investigated in many experiments [26] often using the intervention expressive writing developed by Pennebaker [27]. Structured writing about emotions associated with traumatic events have a positive effect on psychological wellbeing [28]. Expressive writing for new mothers reduced their symptoms of depression and posttraumatic stress [29]. Pre-term birth mothers were randomized to expressive writing or TAU and the intervention was acceptable and reduced post-traumatic stress, depression and improved mental health [30]. A pilot randomized controlled trial (RCT) investigated the effect of a visuo-spatial task (playing tetris) within 6 hours after emergency caesarean section compared with TAU [31]. The study showed significantly fewer intrusive memories in the intervention group compared with the control group 1 week after the intervention. This intervention was acceptable among a majority of participants and is interesting due to its simplicity and to the fact that it is easily administered.

The recommended treatment for PTSD is trauma-focused cognitive behaviour therapy (TFCBT) or eye movement desensitisation reprocessing (EMDR) [32]. TFCBT is the treatment that currently has the strongest research support for PTSD [33]. The theoretical framework for TFCBT involves confronting trauma related emotional distress via exposure that aim at disconfirming the beliefs that underlie and maintain the PTSD symptoms [34]. In particular, in vivo and imaginal exposure aim at disconfirming beliefs and perceptions related to traumatic stimuli (both external and internal). In vivo exposure enables new learning by activating distress and subsequent the experience of being capable of coping with the symptoms. Revisiting and recounting the trauma memory via imaginal exposure reorganizes the memory and generate habituation so that the trauma memory can be revisited without harm. It is suggested that the effect of TFCBT for those with PTSD FC is equivalent to those with PTSD due to other events [35]. There is no specific treatment recommendation for PTSD FC in Sweden but in the United Kingdom and some other western countries the treatment recommendations are based on existing knowledge about treatment of PTSD in general [36, 37].

To the best of our knowledge, no RCT with face to face CBT for women with PTSD FC has been published. A few case studies have investigated the effects of psychological interventions (CBT, EMDR and expressive writing), with positive results, for women with PTSD FC [15, 38–41]. However, one Swedish RCT investigated internet-delivered CBT (iCBT) vs waitlist for women with PTSD FC with recruitment taking place by using a nationwide invitation [42]. The iCBT (trauma focused) consisted of 8 weeks with support, which included feedback on homework assignments. The results (pre-post) showed a large between-group effect size at post (ES, *d* = 1.25) on the PTSD measure and a small but significant ES on depressive symptoms in favour of the iCBT group. The study was underpowered, but the authors conclude that iCBT can be used to help women with childbirth-related PTSD symptoms [42]. Depressive symptoms are common among mothers with or without PTSD or negative experiences. A recent trial investigated the effect of a brief online self-help (cognitive skills for negative beliefs) compared to an active comparison group (time management skills) [43]. There was a significant improvement in mood for the cognitive skills group compared to the control group. The authors conclude that online interventions for negative mood is acceptable and helpful for those without a clinical depression.

In a meta-analysis on iCBT for PTSD due to other events than negative effects of childbirth, medium to large effect sizes were found (0.66 < *g* < 0.83) in favour of iCBT vs passive controls [44]. The authors conclude that iCBT for PTSD is promising and a viable approach for treatment of PTSD. However, more studies with follow-up are needed [44], and the efficacy of iCBT for those with a negative experience needs to be evaluated [9]. Finally, we found no CBT or EMDR study that involved the partners of women with negative experiences or PTSD FC. There is also a need for health economic evaluations when investigating treatment interventions; none of the above-mentioned treatment studies presented this.

The current study addresses gaps concerning treatment for this population. First, the intervention consists of two steps, where step-1 is offered to all women with negative birth experiences, regardless of whether they have a PTSD diagnose or not. Those who fulfil the criteria for PTSD FC after step-1 are offered step-2. Second, the partners are invited to join the treatment in step-1. We also include long-term follow ups. The study involves the partner by facilitating a shared treatment experience with the mother, giving information on how to support her emotionally, and providing practical support that may help her to get the greatest benefit from the treatment program. Finally, we will present a health economic evaluation.

### Aim

The aims of this study are to investigate the effectiveness and cost-effectiveness of iCBT compared with TAU in women with negative birth experiences, posttraumatic stress and PTSD FC, and to investigate whether partner support may add a beneficial effect. The SPIRIT guideline was used.

## Method

### Design

The study is a longitudinal, multi-centre, superiority, randomized controlled trial with two study arms; iCBT+TAU vs. TAU. Primary and secondary outcomes are assessed at baseline, after 6 and 14 weeks and subsequently at 1, 2, 3 and 4 years after end of treatment (Fig. 1).

**Fig. 1 Fig1:**
[figure not shown]
JUNO flow diagram

### Hypothesis

#### Primary

Women who report a negative experience from childbirth and receive iCBT+TAU will report lower levels of posttraumatic stress and depressive symptoms, as well as a smaller proportion of participants classified as fulfilling the criteria for PTSD, and a smaller proportion of participants with postpartum depression according to cut-off compared with those receiving only TAU.

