### Sample size and power

There was a lack of studies for power calculation regarding iCBT for this population at the planning stage of this study. We therefore used information from a study that investigated iCBT for PTSD (due to other events) in a Swedish context [45]. This study had a large effect size on the continuous primary outcome measure (*d* = 1.25) in favour of the treatment group. We estimated a conservative medium effect size (Cohen’s *d* = 0.5), *α* = .05, and a power of 0.8 based on this study. A total sample size of 130 participants is needed for between-subjects t-test contrasts. For categorical outcome measures, a medium effect size (*ω* = 0.3), *α* = .05, df = 1, and a power of 0.8 was used to calculate the needed sample size. A total sample size of 88 participants is needed for *χ*^2^ analysis.

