### Primary outcome measures

*The Traumatic Event Scale (TES)* measures post-traumatic stress symptoms related to childbirth, 3 months after delivery [50]. The scale was developed to assess the DSM-IV [8] criteria for PTSD FC. It comprises the stressor criterion A, with the four items formulated as follows; 1) The childbirth was a trying experience, 2) The childbirth was a threat to my physical integrity, 3) During the childbirth I was afraid that I was going to die, 4) During the childbirth I felt anxious/helpless/horrified. The response options for the A criterion are “not at all, somewhat, much, very much”, The A criterion is met if the alternatives “much” or “very much” is chosen on item 1, 2 or 3, and 4. The three categories of PTSD symptoms (in total 17 items) assess re-experiencing (B-criterion), avoidance (C-criterion), and arousal symptoms (D-criterion). The response options for these three categories are “never/ not at all, rarely, sometimes, often” and to be accounted for as presence of a symptom, the alternatives “sometimes” or “often” are required. In accordance with the DSM-IV one of five B items, three of seven C items, and two of five C items are required to fulfil the criteria respectively. The duration criterion (E) is fulfilled if symptoms have been present for 1 month at least. The influence criterion (F) is met if the degree to which it influenced life was ≥ 6 with regard to at least one of the symptoms. The 17 symptom criteria are summed and higher score indicate higher prevalence of symptoms. The symptom scores have shown good internal reliability (*α* = .84) and split half reliability (.90). The difference between the two study arms as concerns the proportion of participants classified as fulfilling the criteria for PTSD at all assessment points will be reported. Means for the summed symptoms score (criteria B, C, and D) will be compared between the study arms. The TES has been adapted for this particular traumatic event (childbirth) where questions point directly at the childbirth [50]. The scale has been developed and evaluated in a Swedish context and thus is considered clinically relevant.

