*Edinburgh Postnatal Depression Scale (EPDS)* [51] measures symptoms of depression. It consists of 10 items, rated from 0 to 3, where higher summed scores indicate more symptoms of depression. The summed score ranges between 0 and 30 where a higher score indicate more symptoms. A cut-off point of ≥12 for postpartum depression is often used for screening in clinical settings [52] and is used in this study as well. A population-based study on the Swedish version showed good validity in comparison with a clinical interview [52]. The EPDS is a widely used screening measure of post-natal depression with a sensitivity of 86%, specificity of 78%, high standardised Cronbach’s *α* (.87) and split-half reliability (.88) [51]. Between the two study arms, the difference in the proportion of participants with postpartum depression according to cut-off and means for the summed scores at all assessment points will be reported. EPDS is the most frequently used instrument to screen for post-natal depression and its use will enable comparisons between studies.

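### The primary hypothesis has four comparisons and no named visit or success rule, so the single-test 5% error rate and 80% power do not both apply to it

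*Protocol article*

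**What the plan says.** - **Hypothesis, Primary.** Women given iCBT plus TAU "will report lower levels of posttraumatic stress and depressive symptoms, as well as a smaller proportion of participants classified" as meeting PTSD criteria, and a smaller proportion with postpartum depression by cut-off. The four comparisons are the TES level, the EPDS level, the PTSD proportion and the proportion with EPDS of 12 or more. The abstract names two constructs: "The primary outcome measures are symptoms of posttraumatic stress and depression".
- **Design.** Primary and secondary outcomes are "assessed at baseline, after 6 and 14 weeks and subsequently at 1, 2, 3 and 4 years". That gives six post-baseline visits, none singled out.
- **Primary outcome measures.** For TES, the arm difference in the proportion "classified as fulfilling the criteria for PTSD at all assessment points will be reported". The summed TES score is to be compared between arms, with no visit given. For EPDS, the proportion by "cut-off and means for the summed scores at all assessment points will be reported".
- **Sample size and power.** With d = 0.5, alpha .05 and power 0.8, "A total sample size of 130 participants is needed for between-subjects t-test contrasts". With omega = 0.3, df = 1 and the same alpha and power, 88 are needed for a chi-square test.
- **Statistical analysis.** Continuous outcomes go into an MMRM. Binary outcomes get chi-square tests and odds ratios. No primary contrast is named.

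**The concern.** The sample size answers a question about one test, while the primary hypothesis asks about four, each observable at six visits. The article does not say whether one success is enough, all four are needed, or some order applies.

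Each way of filling that gap costs something. If one success is enough, a trial of an ineffective programme has well over a 5% chance of a positive primary claim, and the visit can be picked after the fact. If all four are needed, which is how the conjunctions in the hypothesis most naturally read, a programme that works exactly as assumed has clearly less than an 80% chance of confirming it. A reader of the final report could not tell which standard had been set in advance.

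**Working it through.** **Inputs.** From Sample size and power: d = 0.5, omega = 0.3, alpha = .05, power 0.8, N = 130 and N = 88. From Randomisation: 1:1 allocation. From Hypothesis: four comparisons. From Design: six post-baseline visits. Correlations between test statistics are not in the document. I assume equal correlations from 0 to 0.7, with values above 0 evaluated by simulating correlated normal test statistics.

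**1. The plan's own figures.** Sidedness is not stated. Two-sided is assumed, because one-sided would need only about 100.
- t-test: noncentrality = 0.5 × √(N/4). Power reaches 80% at N = 128 and is 80.8% at N = 130.
- Chi-square: noncentrality = N × 0.3². At N = 88, power is 80.4%.

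Both stated sizes are right for a single test. At N = 130 the chi-square test has power 92.8%.

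**2. Any one of four counts, at one visit.**
- Independent tests: error = 1 − 0.95⁴ = 18.5%.
- Correlation 0.3, 0.5, 0.7: 17%, 16%, 13%.
- Power of this rule under independence: 1 − (1 − 0.808)² × (1 − 0.928)² = 99.98%. At correlation 0.7 it is about 98%.

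Error fails; power does not.

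**3. The visit is left free.**
- One outcome, best of six visits, independent: 1 − 0.95⁶ = 26.5%. At correlation 0.7 between visits: 16%.
- Widest reading, any of 4 × 6 = 24 tests, independent: 1 − 0.95²⁴ = 70.8%. With correlations of 0.3 to 0.7 between outcomes and between visits: about 64% down to 38%.

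**4. All four must succeed, at one fixed visit.** Error is at most 5%. Joint power at N = 130:
- Independent: 0.808² × 0.928² = 0.652 × 0.861 = 56%.
- Correlation 0.3, 0.5, 0.7: 62%, 66%, 70%.

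Power fails; error does not.

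**5. Error held at 5% by Bonferroni.**

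| Family | Level per test | t-test power at N = 130 | N for 80% (t-test) |
|---|---|---|---|
| Two scales | .025 | 71.9% | 156 |
| Four comparisons | .0125 | 62.5% | 182 |

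**6. One outcome at one named visit.** Error 5% and power 80.8% at N = 130, before any loss to follow-up. This is the case the sample size was computed for.

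**The case against.** The strongest reply is that test levels and multiplicity procedures are commonly left to the SAP, which is not shown, and that the article promises to report results at all assessment points, which is not the same as testing each for the primary claim. This stands in part. A procedure may exist elsewhere. But the choice of primary outcome and visit belongs in the protocol, and the four-part hypothesis and single-test sample size are fixed here. A later multiplicity rule cannot make those two agree; the Bonferroni figures show what it would cost.

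Several stronger readings are tempting but are not supported:
- **Both properties fail at once.** A reader might infer that the hypothesis has neither 5% error nor 80% power. Under the any-of-four rule power is well above 80%. Under all four at one visit, error is at most 5%. One or the other fails, depending on a rule the document does not give.
- **Every test is run at .05.** That level appears only as an input to the two sample-size calculations.
- **Twenty-four tests are planned.** This is the widest reading. The MMRM could give one overall test per scale, and the TES mean comparison is not tied to every visit. The binary outcomes have chi-square tests with no overall test across visits, so the choice of visit remains open for them.
- **The all-four reading is nearly sure to fail.** Joint power of 20% to 24% results if d = 0.5 is carried through to the proportions from control rates of 15.7% (a literature figure for high-risk samples in the Background) and 25% (not in the document). Those rates imply omegas of about 0.14 and 0.17. The protocol assumes 0.3, which gives 56% to 70%. Whether 0.3 is plausible is a separate question.

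**Conclusion.** The point holds: the 5% error rate and the 80% power, each computed for a single test, do not both apply to the primary hypothesis as written. With any of four at one visit, error is about 13% to 18.5%. One outcome at the best of six visits gives 16% to 26.5%. With all four required at one visit, joint power is about 56% to 70%.

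The direction does not depend on the assumed correlations, but the exact size does. The power figures also assume that d = 0.5 and omega = 0.3 are true, that 130 women are analysed and that tests are two-sided. The stated sample sizes are themselves correct for one test each.

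**What to change.** Before outcomes are compared by arm:
1. Name one primary visit. Fourteen weeks, after step 2, is one candidate. Six weeks could also be argued, since step 2 is offered only to women who meet PTSD criteria after step 1. The choice is the sponsor's.
2. State one success rule at that visit, for example the TES symptom sum at two-sided .05, then the EPDS sum at .05 only if TES succeeds. Holm across the two scales is an alternative. The planned MMRM can supply both contrasts.
3. Make the two proportions and all other visits secondary, reported with confidence intervals.
4. State that the 0.8 power refers to the single TES contrast at that visit. This fits the fixed order. Under Holm, TES power at N = 130 lies between 71.9% and 80.8%.
5. Log the change in the registry, with its date and whether any data by arm had been seen. The last randomisation was on 12 April 2018 and the article appeared on 1 October 2018, so 14-week data were already due when it was published.

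The cost is a few sentences and no extra participants. The proportions and the other visits lose primary status. In the fixed order, the chance of succeeding on both scales is about 65% (0.808², independent) to 72% (correlation 0.7) if d = 0.5 holds for each.
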